### Intervention

Patients included in the intervention arm will be submitted to an exercise training performed three times a week for 60 min, during a 6-month period. Each session will comprise 30 min of aerobic exercise on a treadmill or cycle ergometer (the first 5 min of warm-up and the last 5 min of cool-down), 20 min of strength exercises for the major muscle groups (sit-ups, push-ups, and pull-ups), and 10 min of stretching. The exercise intensity will be set according to the heart rate obtained during the CPET, corresponding to the anaerobic threshold minus 10 % in the first month of exercise protocol and the anaerobic threshold plus 10 % in the following months. Blood pressure, heart rate, and oxygen saturation will be measured before, during aerobic exercise (at 20 min of aerobic exercise), and at the end of each training session using an aneroid sphygmomanometer (Unitec, São Paulo, Brazil), a heart rate monitor (Polar FT1, Kempele, Finland), and an oximeter (IMFtec®, São Paulo, Brazil). Individuals with long QT syndrome, atrial fibrillation or flutter with ventricular response less than 100 bpm at rest, frequent premature ventricular contractions, sinus tachycardia, sinus bradycardia, or patients with any cardiac related-symptoms will have their rhythm observed with a cardiac monitor during the exercise sessions. Glucose monitoring will be performed before and after exercise sessions in diabetic patients to guarantee its safety. For pre-exercise blood glucose levels of less than 100 mg.dL^−1^ (5.5 mmol.L^−1^), the American Diabetes Association recommends that carbohydrate should be ingested before any exercise. The patient will be able to engage in exercise with levels exceeding 300 mg.dL^−1^ (16.7 mmol.L^−1^) unless they present with ketosis symptoms, or dehydration [15]. All training sessions will be performed in the morning, indoors, and with a controlled temperature environment under supervision of medical staff.

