### Sample size

Considering a difference in peak oxygen intake of 2.9 ml.kg^−1^.min^−1^ with a standard deviation of 2.0 ml.kg^−1^.min^−1^ [38], assuming an *α* = 0.05 and *β* = 0.20, and increasing the sample size by 50 % accounting for losses to follow-up, a total of 30 patients (15 in the control group and 15 in the exercise group) will be included.

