### Statistical analysis

Descriptive analysis will consist of mean and standard deviation for continuous variables and percentage for categorical variables. Skewness and Kurtosis testing will be performed to assess the normality of data which will be log-transformed in case of skewed distribution. Variables that can change prognosis of the disease will be compared at baseline in relation to the exercise and control groups. Longitudinal effects of exercise on primary and secondary outcomes will be evaluated through linear mixed models (LMM), which correlate with repeated measures over the time. LMM is an intention-to-treat analysis as it includes all observations of each one of the patients regardless of losses to follow-up or noncompliance to exercise protocol. The longitudinal analysis will be made by the treatment × time interaction, which estimates the rate of changes in the outcomes. Residual plots of all models will be examined and the likelihood-ratio test will be used to compare and select random intercept or random slope models.

The REDCap software will be used for data management and the data analysis will be conducted by Stata 13.0 software. Statistical significance will be set at *p* < 0.05 for all analyses.

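### The primary effect is framed as a slope over time, is not tied to the VO2 peak difference used for sizing, and can misstate the 6-month effect if the response is non-linear and patients leave after month 3

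*Protocol article*

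**What the plan says.** - **Analysis** (Statistical analysis): primary and secondary outcomes go into linear mixed models. "The longitudinal analysis will be made by the treatment" by time interaction, which the section describes as estimating how fast outcomes change. A likelihood-ratio test chooses between random intercept and random slope models. Every observation is kept, including those of patients later lost.
- **Sizing** (Sample size): "Considering a difference in peak oxygen intake of 2.9 ml" per kg per minute, "with a standard deviation of 2.0 ml" in the same unit, "assuming an *α* = 0.05 and *β* = 0.20". Losses are covered by "increasing the sample size by 50 % accounting for losses to follow-up", giving 15 per arm and 30 in all. No time point is attached to the difference, and no timing to the losses.
- **Visits** (Participants and recruitment; Outcomes): baseline, 3 months and 6 months. None is named as the primary visit.
- **Interim rule** (Interim analysis and stopping rules): it also uses a between-group difference in VO2 peak, not a slope.
- **Training load** (Intervention): heart-rate intensity is set at the anaerobic threshold "minus 10 % in the first month of exercise protocol and the anaerobic threshold plus 10 % in the following months".

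**The concern.** A single interaction that estimates a rate, with random slopes as an option, treats time as continuous and assumes a straight-line response. The sizing and the stopping rule speak of a difference in level. The tested quantity, in ml/kg/min per month, is therefore not linked to the sized difference at any stated visit.

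The link matters when follow-up is incomplete. Patients seen only at baseline and 3 months still inform the slope, and their early change then bears on what is reported for month 6. The Background criticises an earlier study for its short, 3-month follow-up, so the 6-month result is much of what this trial adds. Training intensity is not constant over the six months, so a straight line is not assured.

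**Working it through.** **1. The plan's own sample size.** Two-sided alpha 0.05 (sidedness is not stated) and power 0.80:

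n per arm = 2 × (1.960 + 0.842)² × 2.0² / 2.9² = 7.47, so 8.

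- Dividing by (1 - 0.5): 7.47 / 0.5 = 14.93, so 15 per arm and 30 in total. This matches exactly.
- Multiplying by 1.5: 8 × 1.5 = 12 per arm, 24 in total. From the t-test n of 9: 13.5, so 14 per arm and 28 in total.

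A literal increase of 50% absorbs a loss of 1 - 1/1.5 = one third of those enrolled. The exact match to 30 corresponds to a loss of one half. One third is used below and one half is shown as a variant.

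**2. Complete data.** With visits at 0, 3 and 6 (mean 3), slope = (-3·y0 + 0·y3 + 3·y6) / 18 = (y6 - y0) / 6. Month 3 has no weight, so six times the slope is the 6-month change whatever the shape.

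**3. One third of each arm lost after month 3.** Assumptions: random intercept, within-patient correlation rho, loss unrelated to outcome. Let d3 and d6 be the true between-arm effects at 3 and 6 months (none at baseline). The large-sample estimate solves

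(Σ f X'V⁻¹X) b = Σ f X'V⁻¹d,

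summed over completers (f = 2/3) and patients with two visits (f = 1/3). At rho = 0.5:

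- Left side: [[1, 3], [3, 33]] + [[4/9, 2/3], [2/3, 4]] = [[13/9, 11/3], [11/3, 37]], determinant 40.
- Right side: (5/9·d3 + 1/3·d6 ; 7/3·d3 + 5·d6).
- Slope = (4/3·d3 + 6·d6) / 40, so 6 × slope = 0.200·d3 + 0.900·d6.

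The same steps give 0.2105·d3 + 0.8947·d6 at rho = 0.7 and 0.2149·d3 + 0.8926·d6 at rho = 0.8. In each case the weight on d6 is 1 - w/2, where w is the weight on d3, so

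**error at 6 months = w × (d3 - d6/2).**

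It is zero when the effect is linear (d3 = d6/2) or when follow-up is complete (w = 0).

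| Assumed effect at 3, 6 months | 6 × slope, rho 0.5 / 0.7 / 0.8 | True | Error |
|---|---|---|---|
| Linear: 1.45, 2.9 | 2.90 / 2.90 / 2.90 | 2.90 | 0 |
| Full by month 3, held: 2.9, 2.9 | 3.19 / 3.21 / 3.21 | 2.90 | +10 to +11% |
| Late onset: 0.7, 2.9 | 2.75 / 2.74 / 2.74 | 2.90 | about -5% |

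**4. Sensitivity, for the held effect.**
- All losses before month 3: +1 to +3%.
- One half lost after month 3: 3.43 to 3.47 (+18 to +20%) for rho 0.5 to 0.9.
- One third lost after month 3, with an added random slope at rho 0.7: up to 3.41 at the largest slope variance tried.

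**5. Precision.** With 15 per arm, one third lost after month 3, and 2.0 taken as the standard deviation at each visit (the article does not say whether it refers to a level or a change), the standard error of the 6-month effect is:

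| rho | Linear time | Categorical visit |
|---|---|---|
| 0.5 | 0.83 | 0.84 |
| 0.7 | 0.65 | 0.66 |

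**The case against.** The main objection is that this is a risk, not an error, and that much of it stands.

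- A reader might infer that the slope will misstate the 6-month effect. The article does not support that. The error needs both a non-linear effect and losses after month 3, and the article states neither. Otherwise it is zero or, with losses before month 3, small.
- A reader might take a one-third loss as planned. It is only an inference from the 50% increase.
- A reader might suppose that the model doubles the 3-month change of patients who leave. A likelihood model imputes nothing. Literal doubling would give 2/3 × 2.9 + 1/3 × 5.8 = 3.87 for the held effect, not 3.19 to 3.21.
- A larger error can be produced. If an effect of 2.9 at month 3 fell to 1.45 at month 6, the slope would report 1.89 to 1.92 (+30 to +32%). Nothing in the article suggests fading while supervised training continues. The intensity step comes after month 1, before the first follow-up visit, and if anything suggests a slower start, where the error is about -5%.
- The held-effect error of about 0.3 ml/kg/min is below the standard error. With no effect at any visit and random loss, the slope is unbiased, so no excess of false positives is shown.
- The sizing and the analysis do not flatly contradict each other. The sizing names no visit, and with complete data the two quantities differ only in scale.

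It can also be said that the coding of time belongs in an analysis plan not shown here. That carries less weight, because the article does state the effect measure: an interaction read as a rate, with random slopes as an option.

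**Conclusion.** The point holds as a conditional risk that should be removed. The stated effect measure is a rate of change, the sizing rests on a difference of 2.9 ml/kg/min in VO2 peak, and no primary visit connects them. With complete data or a linear response the choice is harmless. With one third lost after month 3 at random and rho 0.5 to 0.8, the slope gives 3.19 to 3.21 against 2.90 for an effect complete by month 3 and held, and 2.74 to 2.75 against 2.90 for a late one. The loss fraction, its timing, the correlation, the response shape and the random-intercept structure are all assumptions. Linear time is itself inferred from the wording, though it is the natural reading.

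**What to change.** Keep the mixed model and all observations, but fit visit as a categorical factor (baseline, 3 and 6 months) with its interaction with arm. Name one primary contrast: the between-arm difference in VO2 peak change from baseline to 6 months, in ml/kg/min. Make the 3-month contrast secondary, and state that the 2.9 in the sample size refers to the 6-month contrast, if that is what was meant.

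This contrast is unbiased for any response shape when loss is missing at random. It does not protect against loss that depends on unobserved values, and neither does the slope.

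The cost is a change of wording, one more mean parameter per arm (three visit means instead of an intercept and a slope), and the small loss of precision shown in the working. The sample size stays at 30.

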**Methods:**

The PEACH study is a superiority randomized clinical trial which will include subjects who meet the following criteria: Chagas heart disease with a left ventricular ejection fraction below 45 % with or without heart failure symptoms; clinical stability in the last 3 months; adherence to clinical treatment; and age above 18 years. The exclusion criteria are: pregnancy; neuromuscular limitations; smoking; evidence of non-chagasic heart disease; systemic conditions that limit exercise practice or cardiopulmonary exercise test; unavailability to attend the center three times a week during the intervention period; and practitioners of regular exercise. The intervention group will perform an exercise training intervention three times per week during 6 months and will be compared to the control group without exercise. Both groups will undergo the same monthly pharmaceutical and nutritional counseling as well as standard medical treatment according to the Brazilian consensus on Chagas disease. The primary outcome is functional capacity based on peak exercise oxygen consumption during cardiopulmonary exercise testing. Secondary outcomes are: cardiac function; body composition; muscle respiratory strength; microvascular reactivity; cardiac rhythm abnormalities; autonomic function; biochemical; oxidative stress and inflammatory biomarkers; and quality of life. Subjects will be evaluated at baseline, and at 3 and 6 months after randomization. Thirty patients will be randomly assigned into exercise or control groups at a ratio of 1:1.

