#### Cardiopulmonary exercise test

The primary outcome is functional-capacity-based on VO_2_ peak obtained by a CPET using the VO_2000_ gas analyzer (MedGraphics®, St. Paul, MS, USA) with a computerized system Ergo PC Elite (Micromed®, Brasília, Brazil) and a treadmill (Inbramed®, Porto Alegre, Brazil). A blinded evaluator will perform an incremental exercise test using a ramp protocol, tailored to achieve a fatigue limited exercise duration of approximately 8 to 12 minutes. [18]. The workloads will be based on age, gender, height, and weight; adapted to each subject’s physical condition and effort tolerance. Gas and volume calibrations will be executed on the early morning of each test day. Pulmonary gas exchange will be analyzed breath-by-breath and averaged every 10 s. A 12-lead electrocardiogram will monitor heart rhythm during CPET.

The CPET will be limited by symptoms through the subjective fatigue perception scale (Borg modified) ranging from 0 to 10, with 0 representing absence of fatigue and 10 maximum tolerated efforts. The examiner may interrupt the test in case of identification of any harmful hemodynamic response. The recovery phase will be active with walking in a pre-determined velocity of 2 km.h^−1^ and 2 % of inclination.

The following CPET variables will be analyzed: maximum achieved heart hate (HRmax); maximum achieved blood pressure (BPmax); respiratory exchange ratio (VCO_2_/VO_2_); oxygen consumption at peak of exercise (VO_2_ peak); oxygen consumption at anaerobic threshold (VO_2_ AT); oxygen pulse (O_2_ pulse); ventilation slope equivalent to carbon dioxide production (slope VE/VCO_2_); circulatory power (CP); presence of complex ventricular arrhythmias (VA); functional aerobic impairment (FAI); and oxygen uptake efficiency slope (OUES) values.

The VO_2_ peak during exercise will be defined as the greatest value during 30 s before and after maximum effort. The VO_2_ AT will be determined by the point at which expired carbon dioxide increases in a nonlinear fashion relative to the rate of oxygen consumption according to the V-slope method. Ergo PC Elite software will determine the other variables obtained on the CPET.

Before CPET, the rest electrocardiogram will be evaluated to define if the cardiac rhythm is acceptable to perform the exam. The following markers will not be accepted: sustained ventricular tachycardia, second- and third-degree atrioventricular block, atrial or supraventricular tachycardia (more than 100 bpm).

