### Randomization

A sequence will be computer-generated to randomly allocate 30 patients into two groups in a 1:1 ratio (WinPepi version 11). The sequence will be generated in blocks and by strata of CHD classification (B2 and C) by a single researcher not involved in recruitment. Opaque envelopes will be filled in sequentially to either control or exercise group. Block size will be blinded from investigators involved in patients’ recruitment.

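### The treatment × time test, in its usual form, is a change-score comparison; stating a baseline-adjusted model that also carries the B2/C strata would usually be more precise at almost no cost

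*Protocol article*

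**What the plan says.** - **Outcome and visits.** Under Cardiopulmonary exercise test: "The primary outcome is functional-capacity-based on VO_2_ peak obtained by a CPET". The Abstract (Methods) gives the visits: "Subjects will be evaluated at baseline, and at 3 and 6 months after randomization".
- **Test.** Under Statistical analysis, the effect of exercise on primary and secondary outcomes is the treatment × "time interaction, which estimates the rate of changes in the outcomes" from a linear mixed model. A likelihood-ratio test chooses between random intercept and random slope. The only use of baseline that is described is a comparison of prognostic variables between the arms, which is not an adjustment. No covariate is named.
- **Strata.** Under Randomization: "The sequence will be generated in blocks and by strata of CHD classification (B2 and C"). CHD stage does not appear again under Statistical analysis.
- **Planning figures.** Under Sample size: "difference in peak oxygen intake of 2.9 ml.kg^−1^.min^−1^ with a standard deviation of 2.0 ml.kg^−1^.min^−1", "assuming an *α* = 0.05 and *β* = 0.20", "increasing the sample size by 50 % accounting for losses to follow-up", and "a total of 30 patients (15 in the control group and 15 in the exercise group) will be included". The section does not say whether 2.0 is the SD of a change or of a single measurement.

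**The concern.** Randomisation makes the mean baseline VO2 peak equal in expectation in the two arms. A model that lets the arms differ at baseline, and then reads the effect from treatment × time, subtracts the whole observed baseline difference. The efficient amount to subtract is only rho times that difference, when the variances at the two visits are equal. The excess adds noise. With 15 patients per arm, and fewer after losses, chance baseline differences can be sizeable. What is at stake is the width of the confidence interval for the primary effect, and power if the true effect is smaller than planned.

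The design also stratifies by stage while the stated model has no stage term, so analysis and randomisation do not match on the page.

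**Working it through.** **Inputs.** From Sample size: difference 2.9, SD 2.0, α 0.05 (taken as two-sided), power 0.80, 15 per arm. Assumed: 2.0 is the SD of change; rho from 0.5 to 0.9.

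**1. The plan's own figure.** The normal formula gives n per arm = 2 × (1.960 + 0.842)² × (2.0/2.9)² = 7.5, so 8. The noncentral t gives 9 (power 0.823). Adding half gives 8 × 1.5 = 12 or 9 × 1.5 = 13.5, so 14 per arm; 8/(1 − 0.5) gives 16. Exactly 15 is 10 × 1.5. The stated 30 is therefore close to the 28 or 32 that can be derived, and 15/1.5 = 10 is a natural number of completers per arm to examine.

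**2. What the planned test estimates.** With equally spaced visits at 0, 3 and 6 months and complete data, the least-squares slope gives the visits weights proportional to −1, 0, +1. With a free treatment effect at baseline, treatment × time (scaled to 6 months) is therefore the difference between arms in month 6 minus month 0. In 300 simulated trials of 15 per arm the two agreed to within 5 × 10⁻¹⁴.

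**3. Large-sample variance.** With equal variance σ² at both visits, the change score has variance 2σ²(1 − rho) and the baseline-adjusted outcome has σ²(1 − rho²). The ratio is (1 + rho)/2.

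**4. Small-sample variance for ANCOVA.** Estimating the baseline slope multiplies the expected variance by 1 + 1/(2n − 4). At n = 10 this is 1 + 1/16 = 1.0625.

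| rho | (1 + rho)/2 | × 1.0625 |
|---|---|---|
| 0.5 | 0.75 | 0.80 |
| 0.7 | 0.85 | 0.90 |
| 0.8 | 0.90 | 0.96 |
| 0.9 | 0.95 | 1.01 |

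**5. Power, 10 completers per arm, SD of change 2.0.** The change score is computed from the noncentral t. ANCOVA is simulated with its slope estimated and one degree of freedom lost.

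| Effect | Change score | ANCOVA, rho 0.5 | 0.7 | 0.8 | 0.9 |
|---|---|---|---|---|---|
| 2.9 | 0.87 | 0.93 | 0.90 | 0.88 | 0.86 |
| 2.0 | 0.56 | 0.66 | 0.60 | 0.58 | 0.56 |

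With 15 per arm, the change score already has power 0.97 at 2.9. At an effect of 2.0 its power is 0.75, and ANCOVA gives 0.85, 0.80 and 0.78 for rho 0.5, 0.7 and 0.8. The effect of 2.0 is an illustrative smaller effect, not a figure from the article.

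**6. Mixed model with a common baseline mean, and the stage term.** In the same 300 trials (no missing data, rho 0.7 within stage, a stage difference of 1.5 in level), the SD of the estimated effect was:
- planned interaction: 0.559
- planned interaction plus a stage main effect: 0.559
- common baseline mean: 0.518, a variance ratio of (0.518/0.559)² = 0.86
- ANCOVA: 0.528, a ratio of (0.528/0.559)² = 0.89
- ANCOVA plus stage: 0.527

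The stage main effect left the interaction estimate unchanged to within 10⁻¹³. A constant difference in level between B2 and C cancels within each patient.

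**The case against.** The strongest reply is that this reads too much into a condensed article. The text does not say that the arms are free to differ at baseline, and it does not rule out covariates. A treatment × time test is compatible with a model that constrains the baseline means, and covariate lists often sit in an analysis plan. This stands in part: a reader might infer that adjustment is excluded, and the article does not say so. What remains is that the article does fix the test, and the ordinary form of that test is the change-score contrast. The better form has to be stated in order to apply.

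Three further inferences should be resisted.
- **That baseline adjustment always gains precision.** For ANCOVA at 10 per arm it does not; at rho 0.9 it breaks even or loses slightly.
- **That leaving out stage widens the standard error whenever stage predicts VO2 peak.** For this model that is wrong (step 6). Stage can help only if it predicts change in VO2 peak, and the article gives no sign either way.
- **That chance baseline imbalance biases the planned result.** Over repeated randomisation the change contrast is unbiased and its type I error is controlled. The imbalance is the same variance seen from another side, not a second harm.

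It is also fair to say that the planned test meets its 0.80 target on the article's own inputs. The mixed model keeps patients with partial follow-up, so a comparison of 10 completers per arm only approximates the planned analysis.

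**Conclusion.** The point holds as a modest gain in efficiency. The planned test is valid, unbiased and adequately powered for 2.9 with an SD of 2.0, so neither an invalid primary analysis nor an underpowered trial follows from this. Under the stated assumptions, ANCOVA cuts the variance by about 20% at rho 0.5 and 10% at rho 0.7, and by nothing at rho 0.9. Power gains at 10 completers per arm are at most about 6 points for an effect of 2.9 and about 10 points for an effect of 2.0.

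The size rests on rho, which the article does not give, and on reading 2.0 as the SD of change. If 2.0 is the SD of a single measurement, the two readings coincide at rho 0.5, because 2σ²(1 − rho) is then σ². At higher rho the planned power is already higher and there is less to gain.

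The case for including stage is mainly that the analysis should match the stratified randomisation; any gain in precision from it is conditional.

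**What to change.** Prespecify, before unblinding, one baseline-adjusted primary analysis:

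- either the linear mixed model with baseline means constrained equal across arms (no treatment main effect at baseline, treatment × time kept), or ANCOVA of 6-month VO2 peak on baseline VO2 peak;
- CHD stage (B2 or C) in the model. In the mixed model, include stage × visit, or stage × time if time is linear, because a stage main effect alone does not alter the treatment × time estimate;
- the same form for the continuous secondary outcomes.

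The cost is a few sentences of wording and one or two degrees of freedom. Baseline VO2 peak and stage are already collected, so no new data are needed. The article reports that recruitment is still under way and that the analyst is blinded, so the change can be made cleanly.
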